## Abstract

**Introduction::**

Influenza is a major respiratory viral infection of humans with high mortality and morbidity rates and profound economic impact. Although influenza vaccines are generally updated yearly to match the viruses expected in the coming season, genetic mutation and reassortment can result in unexpected novel strains. Therefore, it is important to develop universal vaccines inducing protective immunity to such strains before they appear. This clinical trial is designed to evaluate the safety and immunogenicity of Multimeric-001 (M-001), which contains conserved epitopes of influenza A and B. M-001 is able to induce both humoral and cellular immunity and provides broad strain coverage.

**Methods::**

In a multicenter, randomized, double-blind, and controlled phase IIb trial, 222 healthy volunteers aged 18 to 60 years will be randomized into 3 groups (1:1:1) to receive either 2 intramuscular injections of 0.5 mg M-001 (arm 1), 1.0 mg M-001 (arm 2), or saline (arm 3—placebo), before receiving an investigational (whole virus, inactivated, aluminum phosphate gel [AlPO_4_]-adjuvanted) prepandemic influenza vaccine (H5N1). Primary outcomes are safety and cellular immune responses (cell-mediated immunity [CMI]) induced by M-001, evaluated by multiparametric flow cytometry of intracellular cytokines. The secondary outcome is the serum hemagglutination inhibition (HAI) titer toward the H5N1 vaccine strain. Additionally, exploratory outcomes include evaluation of CMI by quantitative reverse transcription polymerase chain reaction of cytokine mRNA, HAI titers toward H5-drifted strains, serum single radial hemolysis titers toward the H5N1 study vaccine, and the association between CMI markers and antibody response.

**Discussion::**

There is a need for influenza vaccines that give the population a broader protection against multiple strains of influenza virus. M-001 might be such vaccine which will be tested in this current trial as a standalone vaccine and as a pandemic primer. Both cellular and humoral immune responses will be evaluated.

**Trial registration::**

EudraCT number: 2015-001979-46.

## Introduction

1

Influenza is a globally important respiratory viral infection of humans that is easily transmitted from person to person.^[1]^ As well as causing annual epidemics during the winter period, newly emerging variants can result in global pandemics.^[1,2]^ Infection of humans with influenza virus is characterized by symptoms such as a sudden onset of high fever and coughing. Although most symptoms are self-limiting and resolved within 1 week, influenza can cause severe illness such as pneumonia and otitis media due to the primary influenza infection or to a secondary bacterial infection.^[1,3–6]^ Severe illness can result in hospitalizations and deaths, in particular among individuals who are at high risk for complications (e.g., children younger than 2 years of age, adults aged ≥65 years, pregnant women, and patients with a chronic disease or a weakened immune system).^[2,4,6]^ According to the World Health Organization (WHO) up to 3 to 5 million cases of severe illness occur worldwide during an annual epidemic, resulting in 250,000 to 500,000 deaths, depending on the severity of the influenza season.^[6,7]^ In addition to the morbidity and mortality, these annual epidemics have an enormous economic impact, both from the costs of treatment (direct costs) and the high levels of work absenteeism (indirect costs).^[6,7]^ The total estimated cost of an influenza epidemic in industrialized countries may reach 56.7 million euros per million of population.^[7]^

The most (cost)-effective way to prevent influenza virus infection and severe illness is vaccination.^[6,8]^ Vaccines are designed to induce the immune responses that would be normally induced by natural infection, but without causing the disease.^[9]^ Commercially available influenza vaccines contain 2 viral surface antigens, the hemagglutinin (HA) and neuraminidase (NA).^[8,10]^ HA is responsible for both the attachment of the virus to the sialic-acid-containing receptors on the host cell surface and the entry of the virus into the host cells, whereas NA releases newly formed virus particles from the cell surface.^[8,10]^ The vaccines elicit antibodies toward these proteins, thereby limiting or eliminating their function.^[10]^ Many countries recommend yearly vaccination against seasonal flu for individuals who are at high risk for complications and for people who live with or care for high-risk individuals.^[1,6]^ Each year, the WHO recommends which virus strains should be included in the seasonal influenza vaccine, usually 2 circulating strains of the influenza A (H1N1 and H3N2) virus and 1 or 2 strains of influenza B virus (Yamagata and/or Victoria lineage).^[1,2,6,8]^ The seasonal vaccine must be updated every year due to the minor amino acid changes (antigenic drifts) that occur in the HA and NA viral surface proteins.^[1,8,11]^ These antigenic drifts, resulting from genetic mutations during viral replication, occur gradually over time, eventually result in the unpredictable appearance of new virus strains that may not be effectively recognized by the immune system.^[11]^ Occasionally, an abrupt and major change (antigenic shift) in the influenza A virus may occur resulting in the introduction of a completely new influenza A subtype that has not previously circulated among humans.^[1,2,8,11]^ These viruses are introduced either by the direct transfer of an avian influenza virus to humans or by reassortment between human and avian viruses after coinfection of another animal serving as a “mixing vessel” (e.g., ducks and pigs).^[1,12]^ Being entirely novel, such shifted viruses are poorly recognized (if at all) by the pre-existing immunity to other virus and may be highly contagious and highly pathogenic, resulting in a pandemic characterized by many more cases of severe illness.^[1,2,11]^

One of the most important factors, which influences the type and subtype-specific effectiveness of a vaccine, is the degree of similarity between the vaccine virus strains and the circulating strains.^[13]^ A vaccine can reduce the risk of illness by 50% to 60% among the overall population during seasons when most circulating virus strains are similar to the vaccine strains.^[13,14]^ However, the Centers for Diseases Control and Prevention (CDC) in the United States estimated that the vaccine effectiveness for the Northern hemisphere in the 2014 to 2015 influenza season was only 23% (95% confidence interval [CI]: 14–31) in the general population.^[15]^ This low efficacy is considered to be the result of the mismatch between the H3N2 contained in the vaccine (A/Texas/50/12) and the circulating H3N2 virus (A/Switzerland/9715293/13) and resulted in the highest recorded rate of flu-associated hospitalization (266.1 per 100,000) among adults aged 65 and older in the United States since the CDC started tracking data.^[13,15–18]^ This mismatch highlights the need for influenza vaccines that give the population a broader protection against multiple strains of influenza virus: a universal vaccine.^[10,19]^

Multimeric-001 (M-001), developed by BiondVax Pharmaceuticals Ltd. (Israel), is designed to be a universal influenza vaccine that confers immunity and protection against a broad range of influenza viruses. M-001 is a single recombinant protein containing 9 B- and T-cell conserved epitopes (epitopes that do not undergo antigenic change) from the HA, nucleoprotein, and matrix 1 proteins of both the influenza A and B virus strains. The vaccine induces both humoral and cellular immunity.^[20,21]^ In this phase IIb trial, the immunogenicity and safety of M-001 and its administration prior to an aluminum phosphate gel (AlPO_4_)-adjuvanted H5N1 investigational influenza vaccine product (Fluart Innovative Vaccines Ltd., Hungary) will be evaluated in healthy adults (aged 18–60 years). Fluart H5N1 vaccine is highly immunogenic at doses of 6 and 12 μg and hence, a suboptimal dose of the vaccine (3 μg) will be used to evaluate the dose sparing potential of M-001 and to show its ability to enhance immunogenicity of the strain-specific vaccine.^[22]^ The immunogenicity of M-001 both as a standalone vaccine and as a pandemic primer will be evaluated. In addition, the association between the cell-mediated immunity (CMI) markers and the antibody responses will be evaluated as an exploratory endpoint. The safety will be evaluated based on the reported adverse events (AEs) and serious adverse events (SAEs) throughout the whole study period.

## Method/design

2

### Study design

2.1

The study is a multicenter, randomized, double-blind, and controlled phase IIb trial involving 222 healthy volunteers aged 18 to 60 years over a period of 187 days (from screening to study conclusion). Individuals volunteering to participate in the study will be screened before enrollment in the trial. Subject eligibility will be assessed during the screening and written consent will be obtained (Fig. 1). The eligible subjects will be randomized to receive 2 administrations of M-001 at low or high dose, or saline as placebo. All participants will receive an investigational AlPO_4_-adjuvanted, inactivated whole virus prepandemic H5N1 vaccine as a third administration to evaluate whether M-001 has a priming effect. The H5N1 vaccine is based on a clade 1 virus A/Vietnam/1194/04. Each administration will be given intramuscularly (i.m.) 21 ± 2 days apart. Blood samples will be taken from all subjects on days 0 (before the first vaccination), 42 (21 days after the second vaccination), and 63 (21 days after the H5N1 vaccination) for serum and peripheral blood mononuclear cells (PBMCs) to evaluate the influenza-specific cellular and humoral immune responses. Additionally, questionnaires/diaries concerning AEs will be issued on days 0 and 21 to subjects for the collection of solicited (e.g., fever, chills, joint pain, muscle pain, sore throat, fatigue, injection site reactions) and unsolicited AEs. The cards will need to be completed by the subjects and returned on day 21 (second vaccination of study vaccine) and day 42 (H5N1 vaccination). Unsolicited AEs and SAEs will be followed throughout the whole study period and thereby AEs from both the study vaccine and H5N1 vaccine. The study will be conducted at the St. Istvan and St. Laszlo Hospital of Budapest (Hungary) and another Hungarian satellite trial site (Béke Hospital, Budapest).

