#### Primary outcomes

2.5.1

The trial has 2 primary outcomes. The first primary outcome is the cellular immune response elicited by M-001, evaluated by multiparametric flow cytometry analysis in all subjects on days 0 and 42. Multiparametric flow cytometry will be performed after 24 h in vitro stimulation of PBMC with vaccine antigen. Markers including clusters of differentiation 3 (CD-3), CD-4, and CD-8 will be used to define cell lineage, and interferon gamma (IFN-γ), interleukin (IL)-2, IL-4, and tumor necrosis factor alpha (TNFα) will be used to detect specific cytokine responses. The other primary outcome is safety evaluation. This includes the solicited AEs in all subjects until 21 days after the last dosing of the study vaccine and the unsolicited AEs and SAEs in all subjects for 180 days after the first injection. The investigator will assess the intensity of the AE and the relationship between the tested vaccine and the occurrence of the AE (Table 2).

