## Discussion

3

The main objective of this phase IIb trial is to evaluate the safety and immunogenicity of M-001 as a standalone universal vaccine and when used as a primer for a pandemic influenza vaccine. Currently, the standard criterion to determine influenza vaccine efficacy is based on HAI titer.^[25,29,30]^ However, this criterion is not applicable for M-001 since only conserved epitopes without hemagglutination and neutralization capacity are included in it.^[20,25]^ Previous trials using M-001 have shown that it induces influenza-specific cellular immune responses, which are suggested to be important for protection against influenza disease.^[31]^ The vaccine efficacy of M-001 will therefore be evaluated by multiparametric flow cytometry analysis in the current trial. Flow cytometry is chosen because the assay provides a sensitive technique for qualitative and quantitative analyses of cellular immune responses.^[25,32]^ Only 1 blood sample is needed to simultaneously measure CD-3, CD-4, and CD-8 T-cells and the functional markers IFN-γ, IL-2, IL-4, and TNF-α for both CD-4 and CD-8 T-cells responses.^[24,25,33]^ The analysis will be standardized and validated before analyzing the clinical samples. In addition to flow cytometry, detection of IFN-γ and granzyme B mRNA expression by qRT-PCR assay will be performed. This method has recently been shown to be a highly sensitive measure for the detection of CMI in guinea pigs immunized intradermally with heat-inactivated varicella-zoster virus.^[34]^ The ultimate aim is to develop a set of correlates of protection that could improve the translation of immunological data from small clinical trials in humans into conclusions about protective efficacy. Currently large clinical trials are required for assessing vaccine efficacy (reduction of illness), since the incidence of influenza is only ∼5%. If such immunological correlates of protection could be identified, they could serve as a surrogate measure of protection in comparatively small trials.

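### Solicited adverse events stop on day 42, the day of the H5N1 injection, so reactions to the boost rest on unsolicited reports only

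*Protocol article*

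**What the plan says.** All references are to the protocol article.

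- **Injections.** Section 2.1 (Study design) gives M-001 or saline twice, then the H5N1 vaccine to everyone: "Each administration will be given intramuscularly (i.m.) 21 ± 2 days apart". The nominal days are 0, 21 and 42.
- **Diary cards.** In section 2.1, "questionnaires/diaries concerning AEs will be issued on days 0 and 21 to subjects for the collection of solicited" and unsolicited events. The cards are to be "completed by the subjects and returned on day 21 (second vaccination of study vaccine) and day 42 (H5N1 vaccination"). No card is described for issue on day 42.
- **Solicited outcome.** Section 2.5.1 (Primary outcomes) makes safety one of two primary outcomes and includes "the solicited AEs in all subjects until 21 days after the last dosing of the study vaccine".
- **Unsolicited outcome.** Section 2.5.1 also includes "unsolicited AEs and SAEs in all subjects for 180 days after the first injection". Section 2.1 adds: "Unsolicited AEs and SAEs will be followed throughout the whole study period and thereby AEs from both the study vaccine and H5N1 vaccine".
- **Objective.** Section 3 (Discussion) gives the main objective as to "evaluate the safety and immunogenicity of M-001 as a standalone universal vaccine and when used as a primer for a pandemic influenza vaccine". Section 1 (Introduction) likewise says that the safety of M-001, and of giving it before the adjuvanted H5N1 product, will be evaluated.

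**The concern.** The third injection is the only one at which all three randomised arms receive the same product. A difference in reactions there between the M-001-primed arms and the saline-primed arm can be attributed to priming. At the first two injections the arms receive different products, so those data describe the reactogenicity of M-001 itself.

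The question follows from the trial's own rationale. Section 1 uses a deliberately suboptimal H5N1 dose to show that M-001 enhances the response to it. A natural companion question is whether priming also makes fever, muscle pain or injection-site reactions to that vaccine more frequent or more intense. The schedule asks about those terms after injections 1 and 2 but not after injection 3. Boost reactions would have to come from unsolicited reports. These need not capture mild, expected reactions as completely as a card that lists them, and their rates could not be compared with the solicited rates after the earlier injections.

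**Working it through.** **1. End of the solicited window.** The inputs are the second M-001 or saline dose on day 21 (section 2.1) and a window of 21 days after the last study-vaccine dose (section 2.5.1).

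21 + 21 = day 42.

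This equals the last card-return day and the day of the H5N1 injection in section 2.1, so the two sections agree with each other on the nominal calendar.

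**2. Solicited days after each injection, nominal schedule.**

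| Injection | Day | Card issued | Card returned | Solicited days |
|---|---|---|---|---|
| 1 (M-001 or saline) | 0 | 0 | 21 | 21 |
| 2 (M-001 or saline) | 21 | 21 | 42 | 21 |
| 3 (H5N1) | 42 | none described | none described | 42 − 42 = 0 |

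**3. Effect of the ± 2-day interval.** The second dose can fall on days 19 to 23 and H5N1 on days 19 + 19 = 38 to 23 + 23 = 46. If H5N1 is given 19 days after the second dose, the outcome window formally overlaps the boost by 21 − 19 = 2 days. The card is due back at the H5N1 visit, so it would not record those days.

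**4. What is collected after the boost.** Unsolicited events and SAEs run to day 180: 180 − 42 = 138 days, in all arms. Section 2.3 shows that day 63 is already a visit (visit 5), 63 − 42 = 21 days after H5N1, and describes a safety phone call on day 180.

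**5. The other reading of study vaccine.** Section 2.1 names the study vaccine and the H5N1 vaccine separately, which supports step 1. The Abstract and section 2.5.2, however, attach the words study vaccine to H5N1. If section 2.5.1 meant to include H5N1, the solicited window would end on 42 + 21 = day 63, and the cards in section 2.1 would leave days 42 to 63 without an instrument.

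**6. Scale.** Planned injections are 3 × 222 = 666. Those without solicited follow-up number 222 (one third), of which 2 × 74 = 148 are in M-001-primed subjects.

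For what a third card could estimate, take primed (148) against unprimed (74) with a common reaction rate p. The documents give no rate, so p is an assumption shown over a range.

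Half-width = 1.96 × √[p(1 − p)(1/148 + 1/74)], where 1/148 + 1/74 = 3/148 = 0.02027.

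- p = 10%: 1.96 × √(0.09 × 0.02027) = 0.084
- p = 30%: 1.96 × √(0.21 × 0.02027) = 0.128
- p = 50%: 1.96 × √(0.25 × 0.02027) = 0.140

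If the 15% loss in section 2.6 applied in full, each figure would be divided by √0.85 = 0.922, giving about 9, 14 and 15 percentage points.

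**The case against.** A reader might infer that safety as a primer goes unmeasured, or that no comparison after the boost is possible. The documents do not support that. Section 2.5.1 makes unsolicited events and SAEs to day 180 part of the primary safety outcome in all subjects, and section 2.1 says expressly that this follow-up covers the H5N1 vaccine. Rates can be compared between randomised, blinded arms over about 138 days. Nor can one say that subjects are asked nothing after the boost: there is a day 63 visit and a day 180 call, and the article does not say how events are elicited at either. Under-recording of expected reactions is plausible, but the documents neither state nor quantify it.

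It can also be said that the scope is disclosed and deliberate: soliciting reactions only to the test product is a legitimate choice, and sections 2.1 and 2.5.1 agree on it. That answers a charge of error. It does not answer the mismatch with the objective in sections 1 and 3, which covers M-001 given before H5N1 and not only M-001 alone.

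The article is condensed. Figure 1 is not shown and could list a further diary, and the full protocol is not at hand. This limits confidence. Still, the article states issue days, return days and an outcome window, so the point rests on what is written and not on an omitted detail.

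Finally, the interval widths rest on assumed rates and pool the two dose arms. They show what an added card could deliver, not how much information the present plan loses relative to its unsolicited data.

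**Conclusion.** The point holds in a limited form. On the stated schedule, solicited collection ends on the day of the H5N1 injection. Reactions to the boost therefore rest on unsolicited events and SAEs only, and post-boost reactogenicity in primed versus saline-primed arms is not systematically solicited, although safety as a primer is an objective. One third of planned injections is affected.

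This is a worthwhile, inexpensive improvement and not a flaw that invalidates the safety assessment. It assumes that study vaccine in section 2.5.1 means M-001 or saline, as the wording of section 2.1 suggests, and that Figure 1 lists no further diary. If the term was meant to include H5N1, the outcome has a window to day 63 with no card described to fill it. On either reading, sections 2.1 and 2.5.1 need to be reconciled.

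**What to change.** - Issue a third diary card with the same solicited terms at the day 42 visit and collect it at the existing day 63 visit. This gives 21 days after the boost, matching the first two injections.
- Report solicited events after the H5N1 injection by arm, separately from those after injections 1 and 2. This can be an additional safety outcome, so the existing solicited primary outcome need not be redefined.
- Define study vaccine once, and state in sections 2.1 and 2.5.1 which injections the solicited window covers.

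The cost is a small protocol amendment, one more card per subject (222 in all) and its data entry. Because ethics and regulatory approval are already in place (section 2.11), the amendment has to go through those bodies. No new visit is needed, and dosing and clinical management are unchanged. The card has to be in place before subjects reach day 42, since diary data on boost reactions cannot be recovered afterwards.

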**Figure 1 F1:**
[figure not shown]
Flow chart describing the study's design.

### Participants

2.2

Individuals will be recruited using advertising material approved by the ethics committee. Healthy males and females between the ages of 18 and 60 are eligible for study participation (Table 1). Pregnant or breast-feeding women are excluded. Other exclusion criteria include individuals who have received an influenza vaccine or have experienced influenza-like illness within the 6 months prior to the study, those who are receiving medicines or treatments that may affect the evaluation of their immune responses or those who have a history of chronic disease and/or immune system disorder (Table 1). Women of childbearing potential and men must agree to practice adequate contraception throughout the study treatment and for at least up to days 51 and 111 of the trial, respectively, since no reproduction toxicity data are known yet. Furthermore, individuals should be able to understand and comply with the study procedures. In addition, individuals will only be included if the individual provides a signed informed consent form after receiving a detailed explanation of the study protocol prior to any study procedures. In case of uncertainty about the medical status of an individual regarding any of the exclusion criteria mentioned, the primary care physician will be consulted. Consultation of the primary care physician is included in the consent form and only concerns medical information about the exclusion criteria.

**Table 1 T1:**
[figure not shown]
Inclusion and exclusion criteria of individuals.

### Screening and baseline assessment

2.3

Baseline assessment during the screening visit will include demographics (i.e., age, gender, and ethnicity), general physical examination, self-reported medical and medication history, history of influenza vaccination, and alcohol, drug, and cigarette consumption. This is to ensure that subjects enter the trial in a healthy condition. A blood sample will be taken at the screening visit for laboratory tests including hematology (e.g., hemoglobin, hematocrit, total and differential leukocyte count, red blood cell count, platelet count) and serum chemistry (e.g., uric acid, creatinine, cholesterol, triglycerides, sodium, potassium). Subjects having an abnormal result for any of the tests, upon consultation with the principal investigator, would be excluded from the study. In addition to the blood sampling, females will undergo a urine pregnancy test. Each screened subject will receive a sequential, unique 5-digit screening number which they will retain, whether or not they are ultimately randomized to receive treatment. Serum samples from the collected blood at visits 2 and 5 (days 0 and 63) will be stored until the end of the trial when serology will be performed to detect antibodies to the H5N1 virus and against the 2015–2016 circulating influenza virus strains in order to identify subjects having had an asymptomatic influenza infection prior to the start of the trial. On day 180 of the trial, each participant will receive a phone call for safety follow-up and then the study will terminate.

